### Secondary objectives

To evaluate the effectiveness of DSME implemented using EK-DIN through a local community leader group teaching format in reducing cardiovascular risk among known diabetes patients.To compare the effectiveness of EK-DIN in improving the quality of diabetes care between socio-economic categories.To evaluate the cost-effectiveness of the EK-DIN kit when implemented through a community leader format.To assess the quality-of-life impact of a culturally embedded and locally developed novel self-management education module (EK-DIN).

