#### Phase 3: Implementation of the intervention (stepped wedge cluster randomized trial (Sw-CRT))

The community intervention phase of the study will begin with a pilot on 10 known diabetes subjects from a nearby locality. The information gathered through the pilot will be used to further fine-tune the rollout plan. After the pilot, the rollout will target to recruit 350 diabetes patients from among the subjects of the DEDICOM-II survey [4]. It is expected that it will be possible to recruit ~ 12 subjects per cluster from among the 20–30 subjects/cluster recruited for the earlier survey [4]. All earlier clusters and participants will be eligible for recruitment in the proposed study and will be approached for informed consent.

The intervention will be rolled out using the stepped wedge cluster randomized trial format, as summarized in Figs. 2 and 3. As presented in this design, clusters enter the intervention arm sequentially, contributing control and intervention data, unlike traditional cluster-randomized clinical trials. The design involves 5 groups of clusters (6 clusters in each group; 2 each from lower, middle, and higher strata) with sequential cluster group crossover from control to intervention until all are exposed. Each cluster group will be pre-specified based on geographical contiguity. The order of rollout in the cluster groups will be determined by a computer-generated random sequence. The sequence will be concealed in opaque sealed envelopes till use. While blinding is not considered feasible at the participant/field staff level, the laboratory processing, data entry, statistical analysis, and investigators will be blinded to the sequence of intervention.

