**Fig. 3 Fig3:**
[figure not shown]
Trial rollout sequence

As presented in Fig. 3, at Step 0, each cluster group starts as a control condition, with the first cluster group initiating the preparation phase and contributing control data. In Step 1, cluster group 1 enters the intervention period. Three months later, another cluster group (6 clusters) enters the intervention period. This process continues until all clusters enter the intervention. Hence, the stepped-wedge trial design involves 3 months of data in pre-intervention and 18 months in post-intervention conditions for cluster group 1, followed by 6 months in pre-intervention and 15 months in post-intervention conditions in cluster group 2, and so on. All 30 clusters will be completed in 5 steps. The study design has been specifically chosen due to the documented inherent sample size, ethical, logistical, and naturalistic advantages of a wedge cluster rollout [16] and to evaluate the baseline status, impact of intervention, and sustainability of any benefits achieved.

For each cluster group, participants of the DEDICOM-II survey will be invited for recruitment by the research team in accordance with the following selection criteria.

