#### Exclusion criteria

Subjects with cancer, renal, hepatic, or intestinal disease requiring continuing treatment or hospital admission (> 1 week in last 1 year)Subjects with inability to communicate (mental illness or physical disability)

A written informed consent form will be taken from all the participants prior to the recruitment by the research team. A baseline evaluation of eligible participants will be done, including the HbA1c, lipid profile, blood pressure, and compliance to the frequency of processes of care like eye examination, foot examination, and urine testing. A baseline evaluation of the quality of life using the QOLID tool [17] and cost of care will also be conducted. Quarterly evaluations for clinical assessment, blood investigations, and interval morbidity will continue in all groups. In the month preceding rollout in each cluster, a community leader (CL) will be identified.

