### Duration of treatment and follow-up

After the completion of the intervention, the subjects will be retested for the same parameters (including blood tests) every 3 months till the trial endpoint (18 months for cluster group 1). In the follow-up period, ad hoc query resolution and monthly support group/revision rounds will be conducted by the CL in the cluster till the end of the trial. Each participant will be called by telephone for each session to encourage attendance. All participants will undergo quarterly blood sampling, preventive examination compliance, and drug compliance monitoring every quarter by the research team in coordination with the CL. All participants will be provided with a symptom diary to document the medical issues faced by them through the study period and the direct and indirect costs incurred on diabetes care through the study period. All the participants will be recommended to continue the routine diabetes care, including medicines and doctor visits with their existing care provider and/or preventive checks, and will be assessed for quality of life using the pre-validated QOLID tool at baseline and last follow-up [17]. Cost of care data for both groups will be documented using the cost logs to allow for cost-effectiveness calculations. Any noted new morbidity will be referred to the primary care provider, and the intervention advice will be modified in accordance with the medical advice, even if unblinding is required. Data collection from all participants will proceed as planned irrespective of compliance or shift in residence (by virtual means if required). If consent is withdrawn during follow-up, existing data available with the team till the date of withdrawal will be used as available.

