In view of the mounting quantum of evidence, peer-led approaches have gained popularity across the world. However, much of the evidence relates to isolated group-based sessions or peer-led approaches delivered through healthcare facilities or primarily digital interventions. None of the studies reviewed has combined group-based DSME delivered through a community leader with an analogous/complementary digital intervention. Also, there has been limited work from India towards improving the quality of diabetes care using a peer-led approach or digital interventions. The Kerala Diabetes Prevention Program did employ a low-cost-peer-led group education approach in favor of costlier ways. The study documented an improvement in cardiovascular risk factors and HRQOL [33]. Similarly, a trial by Kumar et al. [34] on 300 participants from a hospital in Mysuru found a LSM and medication reminder app to be effective in HbA1c reduction.

A positive result will set the template for a generalizable public health intervention with proven community effectiveness, sustainability, cost-effectiveness, and positive quality-of-life impact. While a negative result will require the testing of alternative approaches, it would still add substantially to existing knowledge on the subject. Given the diverse socio-cultural setting in which the trial is being proposed and the high power of the study, the results (positive or negative) should be widely applicable and have policy implications. The investigators will seek to pursue dissemination of the findings and if positive the refinement and expansion of the intervention to a wider variety of settings.

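### Quality of life is measured only when all clusters are in control and again when all are exposed, so its intervention effect has no concurrent control

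*Protocol article*

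**What the plan says.** All references are to the protocol article.

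- **Objective.** Secondary objectives: "To assess the quality-of-life impact of a culturally embedded and locally developed novel self-management education module (EK-DIN)". Quality of life by QOLID is listed again under Economic, social, and qualitative outcome measures.
- **Schedule.** Duration of treatment and follow-up: participants "will be assessed for quality of life using the pre-validated QOLID tool at baseline and last follow-up". The text after the Exclusion criteria confirms the first occasion ("A baseline evaluation of the quality of life using the QOLID tool").
- **Other visits.** The same text adds: "Quarterly evaluations for clinical assessment, blood investigations, and interval morbidity will continue in all groups". Duration of treatment and follow-up adds preventive-examination and drug compliance to the quarterly content. Neither list includes QOLID.
- **Rollout.** The text under Fig. 3 says that "at Step 0, each cluster group starts as a control condition". Phase 3 describes "sequential cluster group crossover from control to intervention until all are exposed".
- **Timeline.** Fig. 3 text: "3 months of data in pre-intervention and 18 months in post-intervention conditions for cluster group 1", then 6 and 15 months for group 2, and so on. Under Secondary outcomes, exposure at the trial endpoint runs from 6 to 18 months across cluster groups.
- **Intended claim.** The Discussion, like the Abstract, says a positive result will give a template with "proven community effectiveness, sustainability, cost-effectiveness, and positive quality-of-life impact".

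**The concern.** A stepped wedge separates the intervention from calendar time only through occasions on which some clusters are exposed and others are not. HbA1c has such occasions because it is measured every quarter. QOLID, on its stated schedule, has none.

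Any change in quality of life over the trial that has nothing to do with EK-DIN would be counted as intervention effect. Examples are secular change, season, ageing with the disease, or repeated contact with the research team. The schedule is stated outright, and a later analysis plan cannot recover data that were not collected. At stake is one named secondary objective and the policy-facing statement that a positive result would have proven a quality-of-life benefit.

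**Working it through.** **Inputs.** From Sample size considerations: 30 clusters, 5 sequences of 6, 12 subjects per cluster, HbA1c SD 4.3, ICC 0.09, alpha 0.05 (taken as two-sided), power 0.9. From the Fig. 3 text: group g starts at month 3g (3, 6, 9, 12, 15) and the trial ends at 3 + 18 = 21 months. Exposure at the end is 21 − 3g = 18, 15, 12, 9, 6 months, which agrees with Secondary outcomes.

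**1. The plan's own figure.** The article gives no figure for quality of life, so the model was checked on HbA1c: categorical periods, random cluster intercept, 6 periods. Cluster variance τ² = 0.09 × 4.3² = 1.664; variance of a cluster-period mean about it σ² = 0.91 × 4.3² / 12 = 1.402. With I = 30, T = 6, U = 90, W = 1980, V = 330:

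Var = Iσ²(σ² + Tτ²) / [(IU − W)σ² + (U² + ITU − TW − IV)τ²] = 479.0 / (720 × 1.402 + 2520 × 1.664) = 479.0 / 5203 = 0.0921

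SE = 0.303 and power = Φ(1/0.303 − 1.96) = 0.909. The stated 0.9 reproduces, so the same model is used below.

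**2. QOLID with one common baseline (month 0) and month 21.** The fixed effects are two periods and the intervention.

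| Occasion | Period 0 | Period 21 | Intervention |
|---|---|---|---|
| Baseline, all 30 clusters | 1 | 0 | 0 |
| Last follow-up, all 30 clusters | 0 | 1 | 1 |

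The intervention column equals the last-period column: rank 2 of 3. A linear trend with unknown slope does not help (again rank 2 of 3). The change can be attributed to EK-DIN only by fixing the size of the trend, for example at zero, which is the before-after reading.

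**3. QOLID with baseline taken group by group before rollout (months 0, 3, 6, 9, 12) and a common end.** There are six period terms and the intervention. Every baseline is still control and every month-21 score still exposed, so the intervention column again equals the last-period column: rank 6 of 7. If time is forced to be linear, the rank is 3 of 3 and an effect can be estimated. However, the slope comes from baselines over months 0 to 12 and is extrapolated 21 − 12 = 9 months to the end.

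**4. Precision, and what an added occasion buys.** Assumptions, since the article gives none for QOLID: SD 1, ICC 0.09, half of the within-cluster variance persistent within participant, an immediate and constant effect, quarterly occasions at months 0 to 21. For a cluster, V = 0.09·J + (0.91/12)(0.5·J + 0.5·I), and SE is the square root of the intervention element of (ΣX′V⁻¹X)⁻¹.

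| QOLID occasions | Estimable with free periods? | SE (in SD) |
|---|---|---|
| Months 0 and 21 (as planned) | No | none |
| Staggered baseline and 21, linear time imposed | Only through the trend | 0.175 |
| 0, 21 and month 3 or 12 | Yes | 0.106 |
| 0, 21 and month 6 or 9 | Yes | 0.087 |
| 0, 21 and month 15 or 18 | No (all exposed) | none |
| All 8 quarters | Yes | 0.048 |

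Varying the persistent share over 0.3 to 0.8 and the ICC over 0.02 to 0.15 in the same formula moves the month 6 or 9 figure between 0.054 and 0.102, and the all-quarters figure between 0.029 and 0.057. The pattern of what is and is not estimable does not depend on these values.

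A visit in a group's starting month is coded as exposed here. If it is held just before delivery begins, the informative window moves from months 3 to 12 to months 6 to 15. Months 6, 9 and 12 are informative either way.

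**The case against.** **The baseline may not be common.** The article invites participants cluster group by cluster group, and Trial status runs phase 3 recruitment from 1/2/24 to 1/06/2025, about 16 months. Against this, the Fig. 3 text gives group 2 six months of pre-intervention data, and quarterly evaluations are to continue in all groups. The question stays open. A staggered baseline does admit an estimate under an assumed trend shape, so a reader who infers that the objective cannot be answered at all goes further than the document supports. It does not supply concurrent controls, as step 3 shows.

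**Randomisation still contributes something.** The groups reach the end with randomised exposure of 6 to 18 months, and that QOLID contrast is estimable. It would be wrong to say that the rollout order adds nothing. But no group has zero exposure at the end, so the contrast compares durations, not intervention with control.

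**QOLID may be repeated more often.** Duration of treatment and follow-up also says that subjects are retested every three months on the same parameters, and QOLID belongs to the baseline evaluation. With a staggered baseline and quarterly QOLID after rollout, the effect would be estimable (rank 9 of 9). With a common baseline it would not, because clusters in control would still have no QOLID after month 0. The sentence that names QOLID gives two occasions and is the more specific, so it probably governs; the two should be reconciled.

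**The stakes are limited.** This stands. Quality of life is the last of four secondary objectives, is listed apart from the clinical secondary outcomes, and is not expressly promised as a between-group comparison. The claim in the Discussion is conditional on a positive result.

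**Conclusion.** The point holds in this form: on the stated schedule there are no concurrent control data for quality of life. Its intervention effect is confounded with calendar time and can be obtained only as an uncontrolled before-after change over up to 21 months or by assuming something about the secular trend. With a common baseline, the size of the trend must be assumed; with a staggered baseline, its shape. The non-estimability results (2 of 3, 6 of 7) assume unrestricted period effects and QOLID at two occasions only. They need no assumption about variance, and no sample size changes them. The standard errors are illustrative.

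This should be fixed, but it does not threaten the trial. The HbA1c outcome and its power are unaffected.

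**What to change.** 1. Give QOLID to all recruited clusters, including those still in control, at one or more of the existing quarterly evaluations between months 3 and 12. Month 6 or 9 is the best single choice. Every quarter gives the best precision and also works if recruitment turns out to be staggered, when groups not yet enrolled cannot be measured.
2. Amend the QOLID sentence in Duration of treatment and follow-up to match, and say whether baseline is common or by cluster group.
3. State the analysis: calendar-period effects, an intervention term, a cluster random effect and a participant effect for repeated measures. This needs to be written out, because Quantitative data names only the package and function for HbA1c.
4. If extra QOLID rounds are declined, label the result an uncontrolled before-after change and remove the wording about proven positive quality-of-life impact from the Abstract and the Discussion.

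**Cost.** A protocol amendment and some questionnaire burden at contacts already planned. For 360 subjects the present schedule is 2 × 360 = 720 administrations; one added round makes 3 × 360 = 1,080, and all eight quarters 8 × 360 = 2,880. Rounds missed during rollout cannot be collected later, so the change is useful only if made before or during that period.

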### Sample size considerations

The sample size was estimated using the stepped wedge cluster randomized design package (swCRTdesign) in R software (version 4.0.2) [18]. The following information was utilized from our recent DEDICOM-II survey: thirty clusters, a mean HbA1c of 8.9%, standard deviation 4.3, and an intra-cluster correlation of 0.09. Assuming an alpha error of 0.05 and a power of 0.9, it was estimated that a five-step design, using 12 subjects per cluster and with 6 clusters per sequence (2 from each stratum; a total of 360 subjects) will be required to detect a significant mean difference of 1% (~ 10 mmol/mol) in HbA1c level. The study would also be adequately powered (0.8) for comparisons between socio-economic classes with the same consideration using 2 clusters per step per strata.

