### Quantitative data

Change in HbA1c before and after the intervention will be evaluated, accounting for SW-CRT design using the swCRTdesign package for R version 4.0.2 and the swSummary function [18]. The sustainability of the effects will be evaluated using the change in quarterly parameters after the intervention is completed. Differences between socio-economic strata will be compared as sub-group analyses depending on the income category of the clusters. Missing data will not be imputed.

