#### Expected outcomes

##### Primary outcome measure

Comparison of the HbA1c levels between the groups 3 months after the start of intervention.

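### The primary HbA1c comparison names no participant-level term, so HbA1c-related withdrawal at crossover can be read as an intervention effect

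*Protocol article*

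**What the plan says.** Under Statistical analysis, Quantitative data, the protocol article states: "Change in HbA1c before and after the intervention will be evaluated, accounting for SW-CRT design using the swCRTdesign package". It names a package and a summary function, but no regression model and no participant term. The same section adds: "Missing data will not be imputed".

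The section on duration of treatment and follow-up covers people who leave: "If consent is withdrawn during follow-up, existing data available with the team till the date of withdrawal will be used as available". The sentence before it limits other loss: "Data collection from all participants will proceed as planned irrespective of compliance or shift in residence (by virtual means if required".

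The primary outcome is given as "Comparison of the HbA1c levels between the groups 3 months after the start of intervention". The text under Fig. 3 gives "3 months of data in pre-intervention and 18 months in post-intervention conditions for cluster group 1", then 6 and 15 months for group 2, and so on. By extension group 5 has 15 months before and 6 after. The sample size section uses "thirty clusters, a mean HbA1c of 8.9%, standard deviation 4.3, and an intra-cluster correlation of 0.09".

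**The concern.** This is a cohort in which each person is measured quarterly, first unexposed and then exposed. Someone who withdraws at crossover stays in the control data and is absent from the intervention data. If those who leave have higher HbA1c than those who stay, the exposed mean falls with no effect of the education. If they have lower HbA1c, a true benefit is partly hidden.

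A period term removes this only when the loss follows calendar time. Crossover brings fortnightly classes, review of glucose logs and attendance calls, and the classes and log reviews are absent from control quarters. Loss tied to exposure is therefore plausible, though the protocol gives no rate or pattern.

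A paired-change analysis behaves differently. It drops anyone without an after value, and later sequences wait longer before they can supply one.

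**Working it through.** **1. The plan's own power.** Inputs from the sample size section: I = 30 clusters, 12 per cluster, SD 4.3, ICC 0.09, difference 1 point, alpha 0.05 (taken as two-sided), five steps. I take T = 6 periods and a model with a cluster random effect and fixed periods only.
- Between-cluster variance: τ² = 0.09 × 18.49 = 1.664. Residual variance per cluster-period: σ² = 0.91 × 18.49 / 12 = 1.402.
- Design sums: U = 90, W = 1980, V = 330.
- Var = Iσ²(σ² + Tτ²) / [(IU − W)σ² + (U² + ITU − TW − IV)τ²] = 478.98 / (1009.55 + 4193.53) = 0.0921, so SE = 0.303.
- Power = Φ(1/0.303 − 1.96) = 0.909, against 0.90 stated.

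The stated power thus reproduces from a model with a cluster ICC and no within-person correlation.

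**2. Hand check of the raw before/after shift (true effect zero).** Assumptions not in the documents: HbA1c is normal, 70% of within-cluster variance is stable within a person, a fraction f = 10% is lost at crossover, and the chance of loss depends on whether the last value is above or below 8.9.
- Mean distance from 8.9 in either half: 4.3 × √(2/π) = 3.43.
- Share of variance that persists to the next visit: 0.09 + 0.7 × 0.91 = 0.727.
- Shift in the exposed mean = −[f/(1 − f)] × (share of leavers from the upper half − share from the lower half) × 3.43 × 0.727.
- Loss 2:1 towards high values: −0.111 × 0.333 × 2.494 = −0.09.
- Loss 4:1: −0.111 × 0.6 × 2.494 = −0.17.
- All from the upper half: −0.111 × 1 × 2.494 = −0.28.

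**3. Simulation.** 360 people, 8 quarterly visits, zero true effect, 70% stable share, 4:1 selection on the last observed value, 200 replicates, simulation error about 0.015:

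| Analysis | 10% lost at crossover | 20% lost at crossover | 5% per quarter over calendar time |
|---|---|---|---|
| Raw before/after means | −0.17 | −0.41 | −0.29 |
| Cluster and period effects | −0.15 | −0.35 | 0.00 |
| Paired change | +0.05 | +0.11 | +0.03 |
| All data, participant random effect | −0.01 | −0.02 | 0.00 |

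The raw-means result at 10% agrees with step 2. If all of a 10% loss comes from the upper half, with a stable share of 0.6 to 0.8, cluster and period effects give −0.21 to −0.25 and raw means −0.25 to −0.32. With milder selection the cluster-and-period figure falls to about −0.07. A participant effect stayed within about 0.04 of zero throughout. Loss unrelated to HbA1c gave about zero in every analysis tried.

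**4. Unequal loss under paired change.** The primary visit falls at month 6 for group 1 and month 18 for group 5, that is 2 and 6 quarters after a common start. With a constant loss q per quarter, retention is (1 − q)² and (1 − q)⁶.
- q = 2%: 96.0% against 88.6%.
- q = 5%: 90.2% against 73.5%, or 65 against 53 of 72.

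This assumes that everyone enrols at month 0. If later groups enrol nearer their crossover, the gradient shrinks.

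**The case against.** The strongest reply is that the two rules are compatible. A likelihood-based mixed model with a participant effect uses all available data, imputes nothing and accounts for the design. The protocol does not exclude it, and an analysis plan that is not shown may specify it. That stands: there is no contradiction, and declining to impute is not in itself an error. But the article does fix a before/after comparison for its primary outcome, and its power reproduces from a model without a participant term, so a comparison open to this bias is a realistic reading.

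A reader might infer that keeping withdrawn participants' data is the fault. It is not: keeping them is sound and dropping them would be worse. Nor does a paired analysis contradict that rule, since using data as available does not promise that every value enters every comparison.

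The protocol also works to limit loss. Measurement continues whatever the compliance or place of residence, and mop-up and video sessions mean that missing classes is not leaving the study. This makes heavy loss less likely. It does not cover withdrawal of consent, and remote contact cannot supply HbA1c, which the biochemical analysis section obtains from a drawn blood sample taken to the laboratory.

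**Conclusion.** The concern holds in conditional form. Bias in a cluster-and-period analysis needs three things together: loss related to HbA1c, concentrated at crossover, and no participant term. At an assumed 10% loss it is then about −0.07 to −0.25 points, and about −0.1 to −0.3 for raw before/after means, against a 1-point target. The sign reverses if the well controlled leave. These are illustrations, not bounds. They scale with the SD of 4.3 and with a withdrawal rate that the protocol does not give.

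Two stronger conclusions are tempting and unsupported. The documents do not show that a false effect will occur. Nor do they show that unequal loss by sequence destroys comparability: paired change lost more people from later sequences, but its bias under 4:1 selection at crossover was only +0.05 to +0.11.

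**What to change.** In the Quantitative data section, replace the before/after change with one stated analysis. All observed quarterly HbA1c values of every enrolled participant, including those before withdrawal, enter a participant-level model with participant and cluster effects, period effects and the intervention term, without imputation. Nobody is then excluded for lacking an after value. State the assumption this rests on: withdrawal may depend on HbA1c values already observed. Report loss by sequence and by control or exposed quarter, so that readers can see whether it clusters at crossover.

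The cost is protocol or analysis-plan wording and a little more analysis. The quarterly data are already planned, so no visits or participants are added, and the rule on data before withdrawal stays as it is.
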